#### 6.9 Missing Data

The missing mechanism analysis will be performed. The missing data will be imputed using multiple imputation.

(1) Multiple-imputation method will be used to handle missing data under the missing at random assumptions.

(2) Five imputed data sets will be generated for the missing data. The missing values will be imputed using fully conditional specification (FCS) with the Multivariate Imputation by Chained Equations (mice) package (version 3.14.0) for R (version 4.2.1), and we will predictive mean matching (PMM) for the imputation of continuous variables. The baseline characteristics are included as auxiliary variables. Observed values and distributions of imputed data will be compared.

(3) The primary and secondary endpoints of each imputed datasets will be analyzed separately. And combined inferences from five imputed data sets are based on Rubin's rules.

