### 3.6 Statistical analysis

All endpoints will be analyzed in a modified intent-to-treat (ITT) population that excluded patients with incorrect diagnosis (autoimmune diseases other than RA) upon enrolment. Sensitivity analysis will be performed to assess the robustness of the primary analysis using multiple imputation, last observation carried forward imputation, and the worst case scenario imputation. The primary endpoint will also be analysed using the per-protocol (PP) analysis, inverse probability of censoring weighted (IPCW) method. Continuous variables are defined as mean (standard deviation, SD) or median (inter-quartile range, IQR) and will be compared between the two groups using the Student's t-test or Wilcoxon

rank-sum test. Categorical variables are defined as frequency or percentage and compared between the two groups using  $\chi^2$  or Wilcoxon rank sum test, as appropriate. The trend of changes in DAS28-CRP and EULAR responses was calculated from baseline to month 6. Preplanned subgroup analyses will be conducted based on disease activity at baseline. Other subgroup analyses were post hoc. Statistical significance are set at 2-sided  $P < .05$ . All data analyses are conducted using the using the SAS and R.

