### 6.3 Sample Size Determination

1) The rate of DAS28-CRP  $\leq 3.2$  at month 6 is assumed 44.3% in the control group and 52% in the SSDM group; 2) 2-sided  $\alpha$  at 0.05 and power at 90%; 3) 20% attrition rate. The calculation yields a total of 2200 patients. And 2204 is the minimum sample size created by the Random Number Generator.

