#### 6.6 Primary endpoint analysis

The primary outcome is the rate of patients achieving DAS28-CRP (CRP)  $\leq 3.2$  at month 6. The categorical variables are described by frequency or percentage. We will report the differences between the two groups and associated 95% confidence intervals (CIs) using the Cochran-Mantel-Haenszel with adjustment for central effects. A nominal significance level of 0.05 (two-sided) will be applied to all the analyses. The statistical analyses and reporting will follow the CONSORT guidelines.

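### Five imputations with no pre-specified seed leave avoidable Monte Carlo error wherever multiple imputation is used; at least 50 would make it small at no real cost

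*Combined protocol and SAP*

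**What the plan says.** SAP 6.9 (2) fixes the number of imputations: "Five imputed data sets will be generated for the missing data". The method is chained equations in a named version of the R package mice, with predictive mean matching for continuous variables and baseline characteristics as auxiliary variables. SAP 6.9 (3) adds that "The primary and secondary endpoints of each imputed datasets will be analyzed separately" and that "combined inferences from five imputed data sets are based on Rubin's rules". The section gives no random seed, no check of Monte Carlo error and no reason for choosing five.

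Three other places bear on how much this matters:

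- SAP 6.3 builds a "20% attrition rate" into the sample size, so a material amount of missing outcome data is expected.
- SAP 6.6 judges results at a fixed threshold: "A nominal significance level of 0.05 (two-sided) will be applied to all the analyses".
- The documents differ on the role of multiple imputation. SAP 6.9 says "Multiple-imputation method will be used to handle missing data under the missing at random assumptions" and carries this through to the primary and secondary endpoints. Protocol 3.6 says "Sensitivity analysis will be performed to assess the robustness of the primary analysis using multiple imputation", alongside last observation carried forward and a worst-case imputation. SAP 6.6, which defines the primary analysis, does not mention imputation.

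**The concern.** Multiple imputation draws random values, so two analysts with the same data and the same SAP but different seeds get different pooled results. With five imputations, the pooled estimate averages only five draws and the between-imputation variance is estimated on 4 degrees of freedom. Both the estimate and its standard error therefore carry simulation noise.

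The usual defence of a small number is relative efficiency, which is high here. But that describes the variance averaged over repetitions. It does not say how far one trial's p-value or interval shifts when the seed changes. If a result lies near 0.05, the seed can decide on which side it falls. Where imputation serves as a robustness check, the same noise blurs the comparison that it is meant to provide.

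**Working it through.** **The plan's own figure.** Inputs from SAP 6.3: 44.3% versus 52%, two-sided 0.05, 90% power, 20% attrition. With unpooled variance,

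n per arm = (1.960 + 1.282)² × (0.443×0.557 + 0.52×0.48) / 0.077² = 879.6, so 880.

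Then 2 × 880 / 0.8 = 2200, as stated (pooled variance gives 2208). At the planned effect, z = 1.960 + 1.282 = 3.24, and the standard error of the difference is 7.7 / 3.24 = 2.4 percentage points.

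**Assumed input.** The documents give no count of missing month-6 outcomes, so FMI is taken as 0.05 to 0.20, the upper end matching the planned attrition. As an indirect guide, SAP 6.4 (3) gives month-6 per-protocol counts of 968 and 886. If 2,204 were randomised 1:1 (an assumption), 1 − 968/1102 = 12.2% and 1 − 886/1102 = 19.6% lie outside that set. This overstates missingness, because the per-protocol set also drops non-adherent patients.

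**Formulas.** For m imputations of one fixed data set:

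- Seed-to-seed SD of the pooled estimate, in standard errors: √(FMI/m).
- Relative efficiency: 1/(1 + FMI/m). At m = 5 this is 0.990 (FMI 0.05) to 0.962 (FMI 0.20).

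**p-values over seeds.** With the unlimited-imputation variance set to 1, the between-imputation variance equals FMI and is estimated on m − 1 degrees of freedom, and p comes from the t reference with Rubin's degrees of freedom. Simulating many seeds for a data set whose limiting p is 0.05 gives:

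| m | FMI | √(FMI/m) | Middle 95% of p |
|---|---|---|---|
| 5 | 0.05 | 0.100 | 0.031–0.083 |
| 5 | 0.20 | 0.200 | 0.016–0.155 |
| 50 | 0.05 | 0.032 | 0.043–0.058 |
| 50 | 0.20 | 0.063 | 0.036–0.070 |
| 100 | 0.05 | 0.022 | 0.045–0.056 |
| 100 | 0.20 | 0.045 | 0.039–0.064 |

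Hand check for m = 5, FMI 0.20: 1.96 ± 1.96 × 0.20 gives z from 1.57 to 2.35, or p from about 0.117 to 0.019. Noise in the standard error and the t reference widen this to the tabulated range.

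**In percentage points.** With a standard error of 2.4 points, the seed SD of the primary difference at m = 5 is 0.10 × 2.4 = 0.24 to 0.20 × 2.4 = 0.48 points. At m = 100 it is about 0.05 to 0.11 points.

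**Averaged over trials at the planned effect.**

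| m | Two seeds disagree on p < 0.05 (FMI 0.05; 0.20) | Power (FMI 0.05; 0.20) |
|---|---|---|
| 5 | 2.2%; 6.3% | 89.6%; 87.7% |
| 50 | 0.7%; 1.5% | 90.0%; 89.7% |
| 100 | 0.5%; 1.1% | 90.0%; 89.8% |

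**Validity.** Under no effect, type I error at m = 5 is about 5% across FMI 0.05 to 0.20.

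**If the planned effect is observed** (limiting z = 3.24, FMI 0.20), the middle 95% of p at m = 5 is 0.0002–0.017, all below 0.05.

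**Patient-level check.** In simulated data with 1,102 per arm, 20% missing and binary imputation by arm and an assumed baseline stratum, one data set with median p 0.027 at m = 5 had a range of 0.008–0.101 and was significant for 83% of seeds. At m = 50 the range was 0.015–0.036 and every seed was significant. These runs did not use the SAP's predictive mean matching or centre-adjusted Cochran–Mantel–Haenszel analysis, so the figures are illustrative.

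**The case against.** The strongest reply is that five imputations are statistically sound here. Rubin's rules carry the 1 + 1/m term and a t reference, type I error stays at about 5%, and relative efficiency is 96% to 99%. All of that stands. A reader might infer from the 4 degrees of freedom that inference with five imputations is invalid or biased; it is not.

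A second reply is that the headline p-value may not involve imputation at all. Protocol 3.6 places it among the sensitivity analyses, and SAP 6.6 does not mention it. This also stands. It is tempting to say that the primary p-value depends on the seed, but the documents support that only if SAP 6.9 governs.

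Third, the p-value ranges are computed for a result on the threshold, where seed effects matter most, and FMI may be low because baseline characteristics enter the imputation. Hence the lower FMI bound, the averages over trials and the planned-effect result above. Even at FMI 0.05 the range at m = 5 is 0.031–0.083, so the point shrinks but does not vanish.

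Fourth, SAP 6.2 archives analysis procedures and 6.9 fixes software versions, so a seed saved in the program would make the interval exactly reproducible afterwards. To call the interval irreproducible would go too far. What is missing is a seed chosen before the data are analysed, and an analysis that hardly depends on it.

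**Conclusion.** The point holds as a minor, free improvement. Where multiple imputation is used, five data sets leave a seed-to-seed SD of 0.10 to 0.20 standard errors, against 0.03 to 0.06 with 50. At the planned effect, moving from five to 50 cuts disagreement between two seeds from about 2–6% of trials to about 1–1.5% or less, and adds about 0.3 to 2 points of power. The loss is one of precision and reproducibility, not bias.

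The sizes rest on an assumed FMI of 0.05 to 0.20. The consequence for the headline result rests on how SAP 6.9 and protocol 3.6 are reconciled. Two further inferences are not supported. A larger number of imputations does not remove seed dependence, because the error falls only as 1/√m. Nor would the trial's conclusion be at risk if the planned 7.7 points were observed.

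**What to change.** In SAP 6.9 (2) and (3), replace five with at least 50 imputed data sets, preferably about 100. State the random seed, and report the Monte Carlo error of the primary estimate with the result. State in both SAP 6.9 and protocol 3.6 whether multiple imputation is the primary handling of missing outcomes or a sensitivity analysis.

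SAP 6.4 (3) already reports per-protocol counts, so the five-imputation analysis may have been run. If so, report it as planned and set the result with more imputations beside it.

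The cost is computing time and a few words in the SAP. Sample size and significance level do not change.

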#### 6.10 Other analyses plan

Pre-planned subgroup analyses will be conducted based on disease activity at baseline with adjustment by study centers, including

- 1) DAS 28-CRP  $\leq 3.2$  and DAS 28-CRP  $> 3.2$ ;
- 2) DAS 28-CRP  $\leq 3.2$ , 3.2-5.1, or  $> 5.1$ ;
- 3) DAS 28-CRP  $\leq 2.6$ , 2.6-3.2, 3.2-5.1, or  $> 5.1$ ;

Other subgroup analyses will be post-hoc. No adjustments for multiple comparisons will be made for all post hoc analyses, which are considered exploratory.

## Appendix 1. Evaluation of Disease Activity

### 1. DAS28-CRP

DAS28 is calculated on the basis of CPR (DAS28-CRP).

$$\text{DAS28-CRP} = 0.56 * \text{Sqrt}(\text{TJC28}) + 0.28 * \text{Sqrt}(\text{SJC28}) + 0.36 * \ln(\text{CRP} + 1) + 0.014 * \text{GH} + 0.96$$

Sqrt: square root

TJC: 28 Tender joint count

SJC: 28 Swollen joint count

CRP: C-reactive protein

GH: General Health on a 100mm. Visual Analogue Scale.

Interpretation

Remission (REM)  $\leq 2.6$ ;

Low Disease Activity (LDA) 2.6-3.2;

Moderate Disease Activity (MDA) 3.2-5.1;

High Disease Activity (HDA)  $> 5.1$

### 2. EULAR response criteria

| DAS28-CRP at endpoint | DAS improvement   |                   |             |
|-----------------------|-------------------|-------------------|-------------|
|                       | $> 1.2$           | 0.6-1.2           | $\leq 0.6$  |
| $\leq 3.2$            | Good response     | Moderate response | No response |
| 3.2 to $\leq 5.1$     | Moderate response | Moderate response | No response |
| $> 5.1$               | Moderate response | No response       | No response |

### 3. ACR/EULAR Boolean remission

At any time point, patient must satisfy all of the following:

(1) Swollen joint count (SJC)  $\leq 1$

(2) Tender joint count (TJC)  $\leq 1$

(3) Patient Global assessment  $\leq 1$  (on a 0-10 scale)

(4) CRP  $\leq 1\text{mg/dL}$

### 4. Clinical Disease Activity Index (CDAI)

The CDAI is calculated as follows:

$$\text{CDAI} = \text{SJC28} + \text{TCJ28} + \text{PtGA} + \text{PhGA}$$

SJC = Swollen Joint Count

TJC = Tender Joint Count

PtGA = Patient Global Assessment of Disease Activity

PhGA = Physician Global Assessment of Disease Activity

Interpretation

Remission  $\leq 2.8$ ;

Low Disease Activity 2.9-10.0;

571 Moderate Disease Activity 10.1-22.0;

572 High Disease Activity > 22.0

573 **5. Simple Disease Activity Index (SDAI)**

574 The SDAI is a tool for measurement of disease activity in RA that integrates measures of physical  
575 examination, acute phase response, patient self-assessment, and evaluator assessment.

576 The SDAI is calculated as follows:

577  $SDAI = SJC28 + TCJ28 + PtGA + PhGA + CRP$

578 SJC = Swollen Joint Count (0 to 28)

579 TJC = Tender Joint Count (0 to 28)

580 PtGA = Patient Global Assessment of Disease Activity (VAS; 0 to 10 cm)

581 PhGA = Physician Global Assessment of Disease Activity (VAS; 0 to 10 cm)

582 CRP = C-reactive protein in mg/dL

583 Interpretation

584 Remission  $\leq 3.3$ ;

585 Low Disease Activity 3.4-11.0;

586 Moderate Disease Activity 11.1-26.0;

587 High disease activity > 26.0

588 **6. Patient's global assessment of disease activity (PtGA)**

589 The patient's global assessment of disease activity (PtGA) is used to assess the patient reporting disease  
590 activity. The patient will be asked to assess their disease during the past week on a visual analogue  
591 scale (VAS; 0 to 10 cm). The anchors of the instrument include 0 to represent 'the best' and 10 to  
592 represent 'the worst'.

593 **7. Physician's global assessment of disease activity (PhGA)**

594 The physician's global assessment of disease activity (PhGA) is used to assess the physician evaluating  
595 disease activity. The physician will assess a patient's disease activity during the past week on a visual  
596 analogue scale (VAS; 0 to 10 cm). The anchors of the instrument include 0 to represent 'the best' and  
597 10 to represent 'the worst'.

## Appendix 2. 2010 ACR/EULAR RA classification criteria

| Domain | Category                                                                                    | Point score |
|--------|---------------------------------------------------------------------------------------------|-------------|
| A      | Joint involvement (0-5 points) a                                                 |             |
|        | 1 large joint                                                                               | 0           |
|        | 2-10 large joints                                                                           | 1           |
|        | 1-3 small joints (large joints not counted)                                                 | 2           |
|        | 4-10 small joints (large joints not counted)                                                | 3           |
|        | > 10 joints including at least one small joint                                              | 5           |
| B      | Serology (at least one test needed for classification; 0-3 points) b             |             |
|        | Negative RF and negative ACPA                                                               | 0           |
|        | Low positive RF or low positive ACPA                                                        | 2           |
|        | High positive RF or high positive ACPA                                                      | 3           |
| C      | Acute-phase reactants (at least one test needed for classification; 0-1 point) c |             |
|        | Normal CRP and normal ESR                                                                   | 0           |
|        | Abnormal CRP or abnormal ESR                                                                | 1           |
| D      | Duration of symptoms d                                                           |             |
|        | < 6 weeks                                                                                   | 0           |
|        | ≥ 6 weeks                                                                                   | 1           |

The criteria are meant to be applied in patients with at least one swollen joint, after the exclusion of other causes of synovitis. The points from each of domain A through D are added and the sum is considered to be the total score. A total score of  $\geq 6$  is needed to classify a patient as having definite RA.

a Joint involvement refers to any swollen or tender joint on examination, which may be confirmed by imaging evidence of synovitis. DIP joints, first CMC joints and first MTP joints are excluded from assessment. Large joints refer to shoulders, elbows, hips, knees and ankles. Small joints refer to MCP joints, PIP joints, second through fifth MTP joints, thumb IP joints and wrists.

b Negative means less than or equal to the upper limit of normal (ULN); low positive means  $> \text{ULN}$ ; high positive means  $> 3 \times \text{ULN}$ .

c Normal and abnormal are determined by local laboratory standards.

d Duration of symptoms as per patient's self-report.

### Appendix 3. 36-Item Short Form Survey Instrument (SF-36)

**Choose one option for each questionnaire item.**

1. In general, would you say your health is:

- ① Excellent    ② Very good    ③ Good    ④ Fair    ⑤ Poor

2. Compared to one year ago, how would you rate your health in general now?

(1) Much better now than one year ago

(2) Somewhat better now than one year ago

(3) About the same

(4) Somewhat worse now than one year ago

(5) Much worse now than one year ago

(The score is 1, 2, 3, 4, 5 for ①-⑤)

3. The following items are about activities you might do during a typical day. Does your health now limit you in these activities? If so, how much?

(1) Vigorous activities, such as running, lifting heavy objects, participating in strenuous sports

- ① Yes, limited a lot    ② Yes, limited a little    ③ No, not limited at all

(The score is 1, 2, 3 for ①-③ the same below)

(2) Moderate activities, such as moving a table, pushing a vacuum cleaner, bowling, or playing golf

- ① Yes, limited a lot    ② Yes, limited a little    ③ No, not limited at all

(3) Lifting or carrying groceries

- ① Yes, limited a lot    ② Yes, limited a little    ③ No, not limited at all

(4) Climbing several flights of stairs

- ① Yes, limited a lot    ② Yes, limited a little    ③ No, not limited at all

(5) Climbing one flight of stairs

- ① Yes, limited a lot    ② Yes, limited a little    ③ No, not limited at all

(6) Bending, kneeling, or stooping

- ① Yes, limited a lot    ② Yes, limited a little    ③ No, not limited at all

(7) Walking more than a mile

- ① Yes, limited a lot    ② Yes, limited a little    ③ No, not limited at all

(8) Walking several blocks

- ① Yes, limited a lot    ② Yes, limited a little    ③ No, not limited at all

(9) Walking one block

- ① Yes, limited a lot    ② Yes, limited a little    ③ No, not limited at all

(10) Bathing or dressing yourself

- ① Yes, limited a lot    ② Yes, limited a little    ③ No, not limited at all

4. During the past 4 weeks, have you had any of the following problems with your work or other regular daily activities as a result of your physical health?

(1) Cut down the amount of time you spent on work or other activities

- ① Yes    ② No

(The score is 1, 2 for ①-② the same below)

(2) Accomplished less than you would like

- ① Yes    ② No

(3) Were limited in the kind of work or other activities

- ① Yes    ② No

(4) Had difficulty performing the work or other activities (for example, it took extra effort)

- ① Yes    ② No

5. During the past 4 weeks, have you had any of the following problems with your work or other regular daily activities as a result of any emotional problems (such as feeling depressed or anxious)?

(1) Cut down the amount of time you spent on work or other activities

- ① Yes    ② No

(The score is 1, 2 for ①-② the same below)

(2) Accomplished less than you would like

- ① Yes    ② No

(3) Didn't do work or other activities as carefully as usual

- ① Yes    ② No

6. During the past 4 weeks, to what extent has your physical health or emotional problems interfered with your normal social activities with family, friends, neighbors, or groups?

- ① Not at all    ② Slightly    ③ Moderately    ④ Quite a bit    ⑤ Extremely

- 671 (The score is 5, 4, 3, 2, 1 for ①-⑤)  
672 7. How much bodily pain have you had during the past 4 weeks?  
673 ① None ② Very mild ③ Mild ④ Moderate ⑤ Severe ⑥ Very severe  
674 (The score is 6, 5.4, 4.2, 3.1, 2.2, 1 for ①-⑤)  
675 8. During the past 4 weeks, how much did pain interfere with your normal work (including both work  
676 outside the home and housework)?  
677 ① Not at all ② A little bit ③ Moderately ④ Quite a bit ⑤ Extremely  
678 (If neither 7 nor 8 is yes, the score is 6, 4.75, 3.5, 2.25, 1.0 for ①-⑤; if 7 is yes and 8 is no, the score is  
679 5, 4, 3, 2, 1 for ①-⑤)  
680 9. These questions are about how you feel and how things have been with you during the past 4 weeks.  
681 For each question, please give the one answer that comes closest to the way you have been  
682 feeling.  
683 How much of the time during the past 4 weeks...  
684 (1) Did you feel full of pep?  
685 ① All of the time ② Most of the time ③ A good bit of the time ④ Some of the time ⑤ A little  
686 of the time ⑥ None of the time  
687 (The score is 6, 5, 4, 3, 2, 1 for ①-⑥)  
688 (2) Have you been a very nervous person?  
689 ① All of the time ② Most of the time ③ A good bit of the time ④ Some of the time ⑤ A little  
690 of the time ⑥ None of the time  
691 (The score is 1, 2, 3, 4, 5, 6 for ①-⑥)  
692 (3) Have you felt so down in the dumps that nothing could cheer you up?  
693 ① All of the time ② Most of the time ③ A good bit of the time ④ Some of the time ⑤ A little  
694 of the time ⑥ None of the time  
695 (The score is 1, 2, 3, 4, 5, 6 for ①-⑥)  
696 (4) Have you felt calm and peaceful?  
697 ① All of the time ② Most of the time ③ A good bit of the time ④ Some of the time ⑤ A little  
698 of the time ⑥ None of the time  
699 (The score is 6, 5, 4, 3, 2, 1 for ①-⑥)  
700 (5) Did you have a lot of energy?  
701 ① All of the time ② Most of the time ③ A good bit of the time ④ Some of the time ⑤ A little  
702 of the time ⑥ None of the time  
703 (The score is 6, 5, 4, 3, 2, 1 for ①-⑥)  
704 (6) Have you felt downhearted and blue?  
705 ① All of the time ② Most of the time ③ A good bit of the time ④ Some of the time ⑤ A little  
706 of the time ⑥ None of the time  
707 (7) Did you feel worn out?  
708 ① All of the time ② Most of the time ③ A good bit of the time ④ Some of the time ⑤ A little  
709 of the time ⑥ None of the time  
710 (The score is 1, 2, 3, 4, 5, 6 for ①-⑥)  
711 (8) Have you been a happy person?  
712 ① All of the time ② Most of the time ③ A good bit of the time ④ Some of the time ⑤ A little  
713 of the time ⑥ None of the time  
714 (The score is 6, 5, 4, 3, 2, 1 for ①-⑥)  
715 (9) Did you feel tired?  
716 ① All of the time ② Most of the time ③ A good bit of the time ④ Some of the time ⑤ A little  
717 of the time ⑥ None of the time  
718 (The score is 1, 2, 3, 4, 5, 6 for ①-⑥)  
719 10. During the past 4 weeks, how much of the time has your physical health or emotional problems  
720 interfered with your social activities (like visiting with friends, relatives, etc.)?  
721 ① All of the time ② Most of the time ③ A good bit of the time ④ Some of the time ⑤ A little  
722 of the time ⑥ None of the time  
723 (The score is 1, 2, 3, 4, 5, 6 for ①-⑥)  
724 11. How TRUE or FALSE is each of the following statements for you.  
725 (1) I seem to get sick a little easier than other people  
726 ① Definitely true ② Mostly true ③ Don't know ④ Mostly false ⑤ Definitely false  
727 (The score is 1, 2, 3, 4, 5 for ①-⑤)  
728 (2) I am as healthy as anybody I know

- 729 ① Definitely true ② Mostly true ③ Don't know ④ Mostly false ⑤ Definitely false  
730 (The score is 5, 4, 3, 2, 1 for ①-⑤)  
731 (3) I expect my health to get worse  
732 ① Definitely true ② Mostly true ③ Don't know ④ Mostly false ⑤ Definitely false  
733 (The score is 1, 2, 3, 4, 5 for ①-⑤)  
734 (4) My health is excellent  
735 ① Definitely true ② Mostly true ③ Don't know ④ Mostly false ⑤ Definitely false  
736 (The score is 5, 4, 3, 2, 1 for ①-⑤)  
737

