**3. Secondary Objectives**

- (1) The proportion of patients with moderate-to-good EULAR response rate at month 6
- (2) ACR/EULAR Boolean remission rate at month 6 and month 12
- (3) The change in simplified disease activity index (SDAI) at month 6 and month 12
- (4) The change in clinical disease activity index (CDAI) at month 6 and month 12
- (5) The change in tender joint counts at month 6 and month 12
- (6) The change in swollen joint counts at month 6 and month 12
- (7) The change in Hospital Anxiety and Depression Scale (HADS) at month 6 and month 12
- (8) The change in the 36-Item Short Form Survey (SF-36) at month 6 and month 12
- (9) Flare rate at month 6 and month 12 at month 6 and month 12
- (10) The rate of patients achieving DAS28-CRP-CRP  $\leq 3.2$  at month 12
- (11) The numbers and rates of adverse events, either reported by the rheumatologists or resulting from an alert in the SSDM.

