#### 6.7 Major secondary analyses

The secondary endpoints include proportion of patients with moderate-to-good EULAR response rate at month 6 and month 12, ACR/EULAR Boolean remission rate month 6 and month 12, the change in simplified disease activity index (SDAI) month 6 and month 12, the change in clinical disease activity index (CDAI) month 6 and month 12, the change in tender joint count and swollen joint count month 6 and month 12, the change in Hospital Anxiety and Depression Scale (HADS) month 6 and month 12, the change in the 36-Item Short Form Survey (SF-36) month 6 and month 12, and flare rate at month 6 and month 12, the rate of patients with DAS28-CRP (CRP)  $\leq 3.2$  at month 12. The number and rate of adverse events. The normal distribution of the numeric variables will be examined using the Kolmogorov-Smirnov test. SDAI is continuously, while CDAI, swollen joint count, HADS and SF-36 are discrete variables. They will be used as continuous variables in this study. Descriptive data will be compared between the two arms using the student's t test for normally distributed data and Wilcoxon rank-sum test for data that are not normally distributed.

For all categorical secondary endpoints, the differences between the two groups and associated 95% confidence intervals (CIs) will be calculated using the Cochran-Mantel-Haenszel with adjustment for center effects. For non-normal distributed continuous and discrete variables, the differences in medians and associated 95% CIs will be analyzed using quantile regression with adjustment for center effects. The median difference of outpatient visits between the two arms were calculated with the use of the Hodges-Lehmann estimated based on the Mann-Whitney U test.

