**SF-36 score calculation**

| Item  | Score | Item   | Score | Item  | Score | Item   | Score |
|-------|-------|--------|-------|-------|-------|--------|-------|
| 1     |       | 3-(9)  |       | 7     |       | 9-(9)  |       |
| 2     |       | 3-(10) |       | 8     |       | 10     |       |
| 3-(1) |       | 4-(1)  |       | 9-(1) |       | 11-(1) |       |
| 3-(2) |       | 4-(2)  |       | 9-(2) |       | 11-(2) |       |
| 3-(3) |       | 4-(3)  |       | 9-(3) |       | 11-(3) |       |
| 3-(4) |       | 4-(4)  |       | 9-(4) |       | 11-(4) |       |
| 3-(5) |       | 5-(1)  |       | 9-(5) |       |        |       |
| 3-(6) |       | 5-(2)  |       | 9-(6) |       |        |       |
| 3-(7) |       | 5-(3)  |       | 9-(7) |       |        |       |
| 3-(8) |       | 6      |       | 9-(8) |       | Sum    |       |

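### Appendix 3 scores SF-36 items 1 and 2 in the opposite direction to the other items and gives an item 8 rule that cannot be applied, while the SAP does not say which SF-36 score is analysed

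*Combined protocol and SAP*

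**What the plan says.** SAP section 3 lists as a secondary objective "The change in the 36-Item Short Form Survey (SF-36) at month 6 and month 12". SAP 6.7 treats the SF-36 as one variable ("SDAI is continuously, while CDAI, swollen joint count, HADS and SF-36 are discrete variables") and says such variables will be handled as continuous. Neither place names a domain, summary or total score. Protocol 3.3(5) likewise lists only the SF-36.

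The scoring instructions are all in Appendix 3:

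- Item 1 offers "① Excellent ② Very good ③ Good ④ Fair ⑤ Poor" and has no score line directly beneath it.
- Item 2 runs from much better to its last option, "5) Much worse now than one year ago". The line that follows reads "The score is 1, 2, 3, 4, 5 for ①-⑤".
- Item 3, on limitation of activities, has "The score is 1, 2, 3 for ①-③ the same below", where the third option is no limitation.
- Item 8 has a conditional rule that begins "If neither 7 nor 8 is yes, the score is 6, 4.75, 3.5, 2.25, 1.0 for ①-⑤". Its second branch, for item 7 *yes* and item 8 *no*, gives 5, 4, 3, 2, 1.
- The closing table, "SF-36 score calculation", has a cell for every item, including 1 and 2, and ends in a single sum cell. It has no recoding step, no subscales and no transformation.

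**The concern.** A summed questionnaire score is meaningful only if all its items point the same way. Appendix 3 clearly aims at this: the negatively worded questions (9-(2), 9-(3), 9-(7), 9-(9), 10, 11-(1), 11-(3)) are already keyed so that more points mean better health. Items 1 and 2 break the pattern. A patient who rates general health as excellent earns 1 on item 1, while one who fully agrees in item 11-(4) that their health is excellent earns 5. In a sum, the two items cancel part of any improvement shown by the other 34.

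Item 8 is a separate problem. Its rule refers to answers the patient cannot give, so two people scoring from the appendix could reach different values.

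At stake is whether the SF-36 comparison at months 6 and 12 can be reproduced from the plan, and whether the score measures change at full strength.

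**Working it through.** The documents give no SF-36 range, standard deviation or power figure, so there is nothing of the plan's own to reproduce. The check scores every item from the lines printed in Appendix 3.

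**Assumptions.** The line after item 2 covers items 1 and 2. Item 9-(6), which has no line of its own, shares the line after 9-(7). Item 8 uses its first schedule (maximum 6).

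**1. Points at best and worst health, as written**

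| Items | Best health | Worst health |
|---|---|---|
| 1 | 1 | 5 |
| 2 | 1 | 5 |
| 3 (10 items) | 30 | 10 |
| 4 (4 items) | 8 | 4 |
| 5 (3 items) | 6 | 3 |
| 6 | 5 | 1 |
| 7 | 6 | 1 |
| 8 | 6 | 1 |
| 9 (9 items) | 54 | 9 |
| 10 | 6 | 1 |
| 11 (4 items) | 20 | 4 |

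Only items 1 and 2 score higher for worse health.

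**2. Span of the sum**

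- Items 3 to 11 alone: best 141, worst 34, span 107.
- As written: best 141 + 1 + 1 = 143, worst 34 + 5 + 5 = 44, span 99.
- With items 1 and 2 turned round: best 141 + 5 + 5 = 151, worst 34 + 1 + 1 = 36, span 115.
- Loss: 115 − 99 = 16 points, and 16/115 = 13.9%.
- With the second item 8 schedule (maximum 5), the spans are 98 and 114, and 16/114 = 14.0%.

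**3. Effect on a change score.** Let a1 and a2 be items 1 and 2 scored so that higher is better. As printed they contribute (6 − a1) + (6 − a2). So the change as written equals the change with both items aligned, minus 2 × (change in a1 + change in a2).

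- One category better on both items: the two items contribute −2 as written and +2 if both are turned round, a difference of 4.
- If item 1 is turned round and item 2 left out, the same patient gains 1, so the difference is 3.

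**4. If the line covers item 2 only.** Item 1 then has no score. Best is 141 + 1 = 142 and worst 34 + 5 = 39, span 103. With item 2 turned round, best is 146 and worst 35, span 111.

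**5. Item 8.** Items 7 and 8 are graded scales of six and five levels. There are two natural meanings of *yes*:

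- *Yes* means answered: both branches then require item 8 to be unanswered, yet both score the option chosen on item 8.
- *Yes* means pain or interference is present: both branches then require no interference, which is option ①, so options ② to ⑤ never receive a score.

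On neither meaning is there a branch for item 8 being *yes*. The two schedules differ by 6 − 5 = 1, 4.75 − 4 = 0.75, 3.5 − 3 = 0.5, 2.25 − 2 = 0.25 and 1 − 1 = 0 points for options ① to ⑤.

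**6. Item 2 as part of a change score.** It compares current health with a year earlier. At baseline the reference point is a year before enrolment, at month 6 about six months before enrolment, and at month 12 about enrolment itself. The reference point therefore moves between visits.

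**The case against.** Several points on the other side are fair.

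- **No sentence makes the sum the endpoint.** This stands. The link is inferred from a sheet with one total and a SAP with one SF-36 variable. But if another score was meant, the documents do not define it, and the endpoint still needs specifying.
- **Item 1 has no line of its own.** This also stands, as a caveat. The line after item 2 uses the circled markers of item 1, whereas item 2 uses bracketed numbers, so covering both is the natural reading. The alternative leaves item 1 unscored and item 2 still reversed.
- **The effect may be small.** The other 34 items all run one way and carry 107 of the 115 points, and the item 8 schedules differ by at most 1 point. The documents give no standard deviation or expected effect for the SF-36, so the consequence for the between-arm comparison cannot be quantified.
- **The item 7 label is a slip.** Six scores are printed for six options but assigned to ①-⑤. The intended scoring is plain, and only the label needs correcting.

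A reader might go further than the documents allow:

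- *The trial's SF-36 data were mis-scored.* The documents show the instructions, not the scoring that was carried out.
- *The score cannot be interpreted as quality of life.* Too strong: as written it still rises by 99 points from worst to best health.
- *The result is biased towards one arm.* The same rule applies to both arms, and nothing in the text points to a favoured arm.
- *Patients are mis-scored by 8 points.* That takes a two-category improvement on both items (−4 against +4) and counts item 2 as reversed. If item 2 is left out, the same patient scores −4 against +2, a difference of 6. Smaller moves give smaller differences.

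**Conclusion.** The point holds for the plan as written. Appendix 3 scores items 1 and 2 against the direction of all the other items, its item 8 rule cannot be carried out, and the SAP does not say which SF-36 score it analyses. If the sum is the endpoint, its worst-to-best span shrinks from 115 to 99 points (about 14%), and improvement on items 1 and 2 is subtracted instead of added.

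This rests on two inferences: that the sum is the analysed score, and that the shared line covers item 1. If the second fails, item 1 is unscored and the span is 103 against 111. If the first fails, the endpoint is undefined.

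The consequence is dilution or distortion of one secondary endpoint in both arms. The primary endpoint is based on DAS28-CRP and the sample size on its response rates, so neither is affected. It is worth correcting because the remedy is cheap, but it does not threaten the trial's main result.

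**What to change.** In Appendix 3 and SAP 6.7:

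1. State which SF-36 score is the endpoint and how it is built from the items.
2. Give item 1 its own score line in the common direction (Excellent = 5 to Poor = 1).
3. Leave item 2 out of the total, because its reference point moves between visits. At minimum, reverse it.
4. Give item 9-(6) its own score line.
5. Correct the item 7 label to ①-⑥.
6. Rewrite the item 8 rule in terms of the response options that items 7 and 8 actually offer, with a defined score for every combination, including a missing answer.
7. Re-score from item-level data at each visit.

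With item 1 turned round, item 2 left out and an item 8 maximum of 6, the total runs from 34 + 1 = 35 to 141 + 5 = 146, a span of 111.

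The cost is wording in the appendix and SAP and a rerun of the scoring; no new data are needed. The drawback is that the total will differ from the one on the printed score sheet, so the change should be documented.
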